### Recruitment

2.8

Following approval of the study proposal and registration with the Clinical Trial Registry of India (CTRI/2025/12/098832- registered on 10-12-2025), investigators are now recruiting participants at the Regional Cancer Centre, Adyar, Chennai.

## Methods: assignment of interventions

3

### Randomisation & sequence generation

3.1

Participants will be randomised in a 1:1 allocation ratio to receive either the Siddha regimen with SOC or SOC alone using block randomization with randomly varying block sizes. The randomisation sequence will be generated by an independent statistician using validated online randomisation software. Although randomisation will not be stratified, predefined subgroup analyses based on treatment modality to cancer, will be conducted during outcome analysis to explore potential differential treatment effects across these subgroups.

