### Trial design

2.2

This study is designed as a superiority, phase II, randomised controlled, open-label, two-arm parallel-group trial comparing participants with RIOM receiving a Siddha regimen as an adjunct to SOC with those receiving SOC alone. The primary endpoint of the study is the reduction in the incidence of severe RIOM, which will be assessed using RTOG grading scale during the course of radiotherapy and again at six weeks after completion of treatment. Participants will be randomly assigned in a 1:1 ratio (Siddha + SOC Vs SOC alone) using variable block sizes to maintain balance between groups, and allocation concealment will be ensured through the sequentially numbered, opaque, sealed envelope (SNOSE) technique. Subgroup analyses are also planned according to treatment modality, including radiotherapy alone, concurrent chemoradiotherapy, and post-operative radiotherapy. Since the study is designed as an open-label trial, centralised assessment of outcomes will be performed wherever possible to reduce the risk of assessment bias.

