### Sample size

2.7

A study by Kazemiana *et al*. reported that among patients with head and neck cancer receiving benzydamine for the management of RIOM, the occurrence of severe RIOM was 43.6%, compared with 78.6% in the placebo group. Based on findings from our previous unpublished study, a 52% reduction in RIOM grade was observed after 48 days of treatment with TPC mouthwash and GV oral application, and a separate study evaluating TPC with povidone–iodine reported an RIOM occurrence of 10%. Drawing on these findings and clinical expertise, it is assumed that the addition of Siddha regimen to SOC would result in a 15% relative reduction in the occurrence of RIOM compared with SOC alone. Accordingly, assuming a 15% superiority margin, a two-sided significance level of 5%, and 80% power, the calculated sample size is 64 participants per arm. Allowing for an anticipated 20% dropout rate, 80 participants per group will be recruited, resulting in a total sample size of 160 participants. The formula to calculate superiority of proportion is given below.$$m=\frac{\left(Z\;1\;-\alpha +Z\;1-\beta )\;2\;[\pi S\;(1-\pi S\;)+\pi T\;(1-\pi T\;)\right]}{(\pi T\;-\pi S\;-\delta )\;2}$$where,
*δ*: Superiority limit of the difference in Proportionsπ T: Proportion in Test Treatmentπ S: Proportion in Standard Treatmentπ T – π S: Expected difference in proportions*α*: Significance level1 – *β*: Power

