### Statistical methods

4.5

Baseline demographic and clinical characteristics of the participants will be summarised using descriptive statistical methods. Categorical data will be presented as frequencies and percentages, whereas continuous data will be expressed either as mean ± standard deviation or as median with interquartile range, based on the distribution of the data.

The primary outcome of the study, namely the severity of oral mucositis assessed using RTOG and WHO oral mucositis scales, will be analysed by comparing the proportion of participants who develop grade ≥2 mucositis in the two study groups. Depending on the suitability of the data, either the chi-square test or Fisher's exact test will be used for comparison. In addition, weekly mucositis grade distributions will be analysed to observe changes in severity, recovery patterns, and overall trends during treatment and follow-up.

For secondary outcomes, pain intensity measured using VAS will be compared between the groups at each assessment point using either the independent samples t-test or the Mann–Whitney U test, based on the data distribution. Analgesic use, categorised according to WHO three-step analgesic ladder, will be analysed as categorical data and compared between groups using the chi-square test or Fisher's exact test. Rescue medication use will be analyzed as a secondary outcome to compare overall analgesic requirements between the study groups. Laboratory investigations will be summarised descriptively and assessed for safety through appropriate within-group and between-group analyses.

The distribution of continuous variables will be checked using histograms to determine normality. Depending on the nature of the data, either parametric or non-parametric statistical methods will be applied for between-group comparisons. Subgroup analyses based on cancer treatment modalities will also be carried out to explore whether the treatment effects remain consistent across clinically relevant subgroups. However, these analyses will be considered exploratory in nature.

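### The primary test ignores treatment modality after unstratified randomisation; stratifying it would be a cheap gain in robustness and, if modality is prognostic, in precision

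*Protocol article*

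**What the plan says.** Section 3.1 (Randomisation & sequence generation) sets 1:1 allocation in randomly varying blocks and continues: "Although randomisation will not be stratified, predefined subgroup analyses based on treatment modality to cancer, will be conducted during outcome analysis".

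Section 2.2 (Trial design) names the groups: "Subgroup analyses are also planned according to treatment modality, including radiotherapy alone, concurrent chemoradiotherapy, and post-operative radiotherapy". Section 4.5 (Statistical methods) calls these subgroups clinically relevant and their analysis exploratory.

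Section 4.5 also fixes the primary comparison. The outcome "will be analysed by comparing the proportion of participants who develop grade ≥2 mucositis in the two study groups", by chi-square or Fisher's exact test. No stratification factor or covariate is named. (The grade threshold there differs from the grade 3 or higher in section 2.5, Outcomes. That is a separate matter. The figures below refer to severe mucositis, grade 3 or higher, because the 43.6% control rate does.)

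Section 4.1 (Plans for assessment and data collection) has screening review the radiotherapy or chemoradiotherapy details and has a clinical history taken at screening or baseline. Modality can therefore be known before allocation.

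**The concern.** The sentence in section 3.1 sets the subgroup analyses against the absence of stratification, as if one made up for the other. It does not. Subgroup analyses ask whether the effect differs between modalities. They leave the overall comparison exposed to any chance difference in modality mix between the arms.

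If modality affects the risk of severe mucositis, two things are lost. First, the unadjusted test carries between-modality variation as noise and so has less power than a stratified test on the same patients. Second, if the arms do come out unbalanced, the only remedy left is an adjustment chosen after the imbalance has been seen. That is easy to contest, the more so in an open-label trial.

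**Working it through.** **Inputs from the protocol article (section 2.7 unless noted).**
- Control rate: "the occurrence of severe RIOM was 43.6%, compared with 78.6% in the placebo group" (43.6% is the benzydamine figure).
- Effect: the Siddha regimen "would result in a 15% relative reduction in the occurrence of RIOM compared with SOC alone", so 0.85 × 43.6% = 37.06%, a difference of 6.5 points.
- Size: "assuming a 15% superiority margin, a two-sided significance level of 5%, and 80% power, the calculated sample size is 64 participants per arm".
- Recruitment target: 80 per arm, which is the 64 raised to cover 20% dropout.
- Allocation 1:1 (section 3.1).

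**The plan's own figure.** The printed formula with πS = 0.436, πT = 0.3706 and a margin of 0.15 that adds to the difference (0.0654 + 0.15 = 0.2154), at one-sided 5%, gives

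(1.645 + 0.842)² × (0.436 × 0.564 + 0.3706 × 0.6294) / 0.2154² = 63.85, so 64; and 64 / 0.8 = 80.

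At the stated two-sided 5% the same formula gives 81.1, so 82. A plain two-sided superiority test of 43.6% v 37.06% needs 880 per arm, and its power at 80 per arm is about 13%. This is a separate and larger problem. It matters here because it sets the baseline against which any gain from stratifying must be read.

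**Assumptions.** The article gives neither the modality shares nor a severe-mucositis rate for any of the three modalities. Assumed shares are 25% radiotherapy alone, 50% chemoradiotherapy and 25% post-operative, with a common odds ratio across modalities. Control rates are varied from no prognostic effect to a very strong one, each averaging 43.6%.

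**Power at 80 per arm, two-sided 5%, unadjusted chi-square v modality-stratified Cochran–Mantel–Haenszel (CMH) test (40,000 simulated trials per case).**

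| Assumed control rates (RT alone / chemo-RT / post-op) | 43.6% v 37.1% | 43.6% v 28.6% |
|---|---|---|
| None (43.6% throughout) | 12.8% v 13.1% | 50.6% v 50.1% |
| Moderate (25 / 55 / 39%) | 12.9% v 13.9% | 51.1% v 52.8% |
| Strong (15 / 65 / 29%) | 12.8% v 15.2% | 50.9% v 58.0% |
| Very strong (5 / 75 / 19%) | 12.7% v 18.4% | 50.9% v 68.6% |

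The last column is a 15-point difference, shown for range.

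A second assumed mix (25 / 45 / 30%) at the 15% relative reduction gives 12.5% v 13.3% with control rates 25/55/40%, 12.6% v 14.7% with 15/65/35%, and 13.0% v 15.9% with 10/70/30%.

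With 64 per arm and no prognostic effect, stratifying costs a little: 12.3% v 11.5% at 37.1%, and 43.6% v 41.9% at 28.6%.

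**Validity.** With no treatment effect, the unadjusted test rejected in 4.6–5.2% of simulated trials and CMH in 4.9–5.2%.

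**Chance imbalance.** With a 50% chemoradiotherapy share, the SD of the between-arm difference in share is √(2 × 0.5 × 0.5 / 80) = 0.079. The normal approximation for a difference of 10 points or more is P(|Z| ≥ 0.10 / 0.079) = 21%. The exact binomial probability of a difference of 8 or more patients out of 80 is 24%.

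A 10-point swap between chemoradiotherapy and radiotherapy alone moves the crude difference by 0.10 × (55 − 25) = 3 points in the moderate case and 0.10 × (65 − 15) = 5 points in the strong case. The planned effect is 6.5 points.

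Among simulated null trials with an imbalance that large (second mix), the unadjusted test rejected about 6%, 8% and 10% of the time for rates 25/55/40%, 15/65/35% and 10/70/30%. CMH stayed near 5%.

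**The case against.** The strongest reply is that nothing here is wrong. Randomisation makes the unadjusted test valid, chance imbalance is already part of its sampling variation, and the simulated type I error confirms this. That stands. A reader might infer that the primary result would be biased or the error rate inflated. Over all possible allocations, neither is so.

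A reader might also infer from section 1.1 that modality is strongly prognostic, since it reports mucositis in 90–100% of chemoradiotherapy patients. The document does not support that reading. The figure is for any mucositis, not severe mucositis, and it is set against about 40% with chemotherapy alone, which is not a modality in this trial. The Discussion gives over 90% for high-dose treatment without separating radiotherapy from chemoradiotherapy. Prognostic strength is therefore an assumption.

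It is tempting, too, to quote larger power gains. With a common odds ratio of 0.35 the gain reaches 6 to 10 points in the stronger scenarios. But that odds ratio implies an 18–21 point difference, about three times the planned 6.5 points, and it has no source in the article.

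Finally, an article may leave a supportive adjusted analysis, and the definitions of the modality groups, to the full protocol or analysis plan. That is fair. So the possible overlap between post-operative radiotherapy and chemoradiotherapy is something to settle when strata are defined, not a fault. The choice of primary test is different, because the article itself fixes it as unadjusted.

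**Conclusion.** The point holds as a recommendation on efficiency and robustness. The plan has an unstratified allocation, an unadjusted primary test, and a baseline factor that it regards as clinically relevant but uses only for exploration. At the plan's own effect the power gain is about 0–3 points for null to strong prognosis and about 6 if very strong. At a 15-point difference it is about 0–2 points (null to moderate), 7 (strong) or 18 (very strong). All of these rest on assumed shares and rates by modality.

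The firmer argument is protection against imbalance. An imbalance of 10 points or more would arise in roughly one trial in four or five, and under the moderate and strong assumptions it would move the crude difference by about half to three quarters of the planned effect (3 / 6.5 = 46%; 5 / 6.5 = 77%). Stratifying does not rescue a trial with about 13% power at its stated effect.

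**What to change.** Pre-specify the primary analysis as a Cochran–Mantel–Haenszel test, reported with a stratified risk difference and 95% CI. Stratify by concurrent chemotherapy as planned at randomisation (yes/no) and, if the strata are not too sparse, by post-operative status (yes/no). Two yes/no factors avoid the question of where a post-operative patient on chemotherapy belongs. State in advance when the strata collapse to chemotherapy yes/no. Keep the unadjusted chi-square or Fisher's exact test as a sensitivity analysis, and say that the modality subgroups address effect heterogeneity only.

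The cost is a change of wording. The allocation list is untouched. Chemotherapy status comes from the screening review. Post-operative status is not named there, so check that the case record form captures it. Because recruitment is under way and interim analyses are planned, date the change before any outcome data are seen by arm. The price is the collapsing rule, essentially no gain if modality is not prognostic, and in that case a power loss of under 2 points with 64 per arm.

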### Allocation concealment mechanism

3.2

Allocation concealment will be ensured using SNOSE method. The envelopes will be prepared by an independent statistician not involved in participant recruitment or outcome assessment. All envelopes will be identical in appearance and tamper-proof. The sealed envelopes will be opened one after another only after participant eligibility has been verified and written informed consent has been obtained. Although the trial will be conducted in an open-label method, outcome assessment may be centrally reviewed where feasible to minimise bias.

### Implementation

3.3

An independent statistician will prepare the randomisation sequence. Participant enrolment and assignment to study groups will be carried out by the study investigator at the recruitment site after confirmation of eligibility and obtaining written informed consent.

### Blinding

3.4

Considering the nature of the intervention, blinding will not be possible. However, to reduce the risk of assessment bias, outcome evaluation will be carried out by trained assessors who are not involved in treatment allocation or intervention administration and are unaware of the participants' group allocation. Participants will be instructed not to disclose their allocation during assessment visits, and clinical assessments will be completed before application of the topical intervention at each visit. Data analysis will be conducted using coded group identifiers.

## Methods: data collection, management and analysis

4

### Plans for assessment and data collection

4.1

Potential participants will be screened by trained investigators to ensure compliance with the inclusion and exclusion criteria. Screening will include a review of medical records and current radiotherapy or chemoradiotherapy details to confirm the diagnosis of head and neck cancer. Eligible participants will be informed about the study objectives, procedures, risks, and benefits, and written informed consent will be obtained prior to enrolment. All screening details will be documented in the screening form and case record form (CRF), with reasons recorded for screen failures. Participants meeting eligibility criteria will proceed to baseline assessments, randomisation, and initiation of the allocated intervention.

At the screening or baseline visit, detailed clinical and drug histories will be recorded. Clinical examination will then be performed to assess the oral mucositis severity using the RTOG and WHO Oral Mucositis Scales during baseline visit. Baseline laboratory investigations, including complete blood count (CBC), liver function test (LFT), and renal function test (RFT), will be performed. Participants will then be randomised, and study medications will be dispensed as per group allocation. Follow-up assessments will be conducted weekly by trained assessors throughout the course of radiotherapy, with telephonic follow-up continued up to six weeks post-radiotherapy. The severity of oral mucositis will be assessed using RTOG and WHO oral mucositis scales, pain intensity will be measured using a 10-point VAS, and analgesic use will be documented according to WHO three-step analgesic ladder. Details of the grading criteria for all these four scales are presented in Table 3. However, in certain clinical situations, analgesics, particularly opioids, may be prescribed for cancer-related pain rather than for RIOM. In such cases, the indication for analgesic use may not directly reflect RIOM severity. To address this, all analgesic usage will be documented along with the primary indication, and cases where analgesics are administered for non-RIOM-related pain, will be clearly specified with appropriate justification. All assessors and physicians involved in outcome evaluation will be trained in advance regarding grading scales and assessment procedures.

**Table 3 T3:** Assessment scales used for outcome evaluation.

Assessment Tool	Grade/Scale	Grading Description
RTOG Oral Mucositis Scale	Grade 0	No change
	Grade 1	Irritation/ Mild pain not requiring analgesics
	Grade 2	Patchy mucositis with inflammatory serosanguinous discharge/ moderate pain requiring analgesics
	Grade 3	Confluent fibrinous mucositis/ severe pain requiring narcotic analgesics
	Grade 4	Ulceration, haemorrhage, or necrosis
WHO Oral Mucositis Scale	Grade 0	No oral mucositis
	Grade 1	Erythema and soreness
	Grade 2	Ulcers present & able to eat solid food
	Grade 3	Ulcers present& requires liquid diet due to mucositis
	Grade 4	Ulcers present; alimentation not possible due to mucositis
VAS for Oral Cavity Pain	0	No pain
	1–3	Mild pain
	4–6	Moderate pain
	7–10	Severe pain
WHO Three-Step Analgesic Ladder	Step 1	Mild pain; Non-opioid analgesics (paracetamol, NSAIDs) ± adjuvants
	Step 2	Mild to moderate pain; Weak opioids (e.g., codeine, tramadol) ± non-opioids and/or adjuvants
	Step 3	Moderate to severe pain; Strong opioids (e.g., morphine, fentanyl, oxycodone) ± non-opioids and/or adjuvants

To evaluate treatment response over time, the percentage distribution of grades/scores obtained from the four above mentioned scales will be assessed separately for each study arm at weekly intervals during study period. These assessments will help compare the severity of mucositis, recovery patterns, pain levels, and analgesic requirements between the two groups over the course of treatment and follow-up. Certain practical limitations may arise while applying the WHO oral mucositis scale in specific clinical situations. For example, some patients may already be receiving nutrition through a nasogastric (NG) tube due to tumour-related obstruction, poor nutritional status, or severe RIOM. In such cases, oral intake is restricted to liquids irrespective of the actual severity of mucositis, which could result in overestimation of the grade, such as categorizing the condition as Grade 3 despite the absence of corresponding clinical findings. To avoid such misclassification, these cases will be recorded as “Not Applicable” for WHO grading, along with proper justification in the study records.

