### Outcomes

2.5

The primary outcome of the study is the severity of RIOM, assessed using RTOG grading scale. This will be measured as the proportion of participants who develop severe oral mucositis (RTOG grade ≥ 3) at any time during radiotherapy and up to six weeks following completion of radiotherapy, compared between the two study arms. The primary outcome will be assessed from randomisation until the last day of study medication use.

The secondary outcomes include oral mucositis severity assessed using WHO oral mucositis scale, measured as the proportionate reduction in the occurrence and severity of mucositis during radiotherapy and up to six weeks post-radiotherapy. Oral cavity pain, evaluated using VAS as the proportion of participants achieving a minimum two-point reduction in pain intensity and analgesic usage, assessed as the percentage of participants requiring analgesics categorised according to WHO three-step analgesic ladder. Safety outcomes will be evaluated by documenting the number of adverse events reported in each study group. Treatment interruption will be assessed as the proportion of participants experiencing one or more radiotherapy interruptions due to severe RIOM and the total number of days of missed radiotherapy. In addition, body weight changes during radiotherapy, requirement for nasogastric tube feeding, and interruptions in oral intake will be documented as exploratory indicators of nutritional impact. All secondary outcomes, except treatment interruption, will be assessed from randomisation until the last day of study medication use, while treatment interruption will be evaluated until the completion of radiotherapy.

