### Participant timeline

2.6

Participants will undergo initial screening and randomisation at baseline, followed by a 14-week observation period comprising weekly clinical evaluations and periodic laboratory assessments as detailed in the timeline below (Table 2).

**Table 2 T2:** Schedule of enrolment, interventions, and assessments.

Activity/Assessment	Baseline	W1	W2	W3	W4	W5	W6	W7	W8	W9	W10	W11	W12	W13
Enrolment														
Screening & Informed Consent	X													
Randomisation & Allocation	X													
Intervention														
Study Intervention	X	X	X	X	X	X	X	X	X	X	X	X	X	X
Efficacy Assessment														
RTOG Scale	X	X	X	X	X	X	X	X	X					X
WHO oral mucositis Scale	X	X	X	X	X	X	X	X	X	X	X	X	X	X
VAS		X	X	X	X	X	X	X	X	X	X	X	X	X
WHO 3-step analgesic ladder		X	X	X	X	X	X	X	X	X	X	X	X	X
Interruption of RT		X	X	X	X	X	X	X	X					
Days of Missed RT		X	X	X	X	X	X	X	X					
Safety & Laboratory Assessment														
Safety Monitoring		X	X	X	X	X	X	X	X	X	X	X	X	X
CBC	X								X					X
LFT	X								X					X
RFT	X								X					X

RT, radiotherapy; RTOG, Radiation Therapy Oncology Group; WHO, World Health Organization; VAS, visual analogue scale; CBC, complete blood count; LFT, liver function test; RFT, renal function Test; W1−13, No. of week.

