### Plans to promote participant retention & complete follow-up

4.2

Participant retention will be promoted through regular in-patient engagement during the radiotherapy admission period, enabling close follow-up, supervision of interventions, and minimising participant burden. During the post-radiotherapy period, follow-up will be ensured through scheduled telephonic contacts. Participants and caregivers will receive counselling on the importance of adherence and follow-up, and family caregivers will be trained during radiotherapy to support intervention use after discharge. Reminder calls will be made prior to scheduled visits, and contact details will be verified at enrolment. In the event of missed visits, study staff will attempt prompt telephonic follow-up to collect outcome data wherever feasible, thereby minimising loss to follow-up.

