### Ancillary and post-trial care

6.5

After completion of RT period, participants in both study arms will be followed for an additional 6weeks, during which the assigned treatments will be continued. Follow-up assessments will be conducted weekly via telephone to monitor recovery and document relevant outcomes.

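### WHO mucositis grades are due weekly for six weeks after radiotherapy, but that follow-up is described as telephonic and the grades need a mucosal finding

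*Protocol article*

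**What the plan says.** **What is scheduled.** Section 2.5 defines the WHO secondary outcome as "measured as the proportionate reduction in the occurrence and severity of mucositis during radiotherapy and up to six weeks post-radiotherapy". In Table 2 (section 2.6) the row "WHO oral mucositis Scale" is marked at baseline and at every week from W1 to W13. RTOG is marked at baseline, W1 to W8 and W13. Blood tests are marked at baseline, W8 and W13. Section 4.1 adds that the distribution of grades on all four scales "will be assessed separately for each study arm at weekly intervals during study period", and section 4.5 uses the weekly mucositis grades to describe severity and recovery.

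**How contact is made after radiotherapy.** Section 4.1 has weekly assessments during radiotherapy, "with telephonic follow-up continued up to six weeks post-radiotherapy". The next sentence names the RTOG and WHO scales without separating attended from telephone contacts. Section 4.2: "During the post-radiotherapy period, follow-up will be ensured through scheduled telephonic contacts". Section 6.5: "Follow-up assessments will be conducted weekly via telephone to monitor recovery and document relevant outcomes".

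**What implies attendance.** Section 2.6 speaks of "weekly clinical evaluations and periodic laboratory assessments as detailed in the timeline below". Section 2.4.3 counts remaining medicine packs at follow-up visits. Section 4.2 mentions reminder calls before visits. Section 4.3 has post-radiotherapy visit dates entered in a patient diary.

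**Recovery.** Section 2.4.2 defines recovery as Grade 0 on both scales. Sections 2.4.1 and 2.4.2 end assessments at recovery if it comes before the planned end.

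**The concern.** In Table 3, WHO Grade 1 requires erythema and Grades 2 to 4 require ulcers. Grades 2 to 4 are then separated by what the patient can eat. A telephone caller can ask about diet, soreness and sores but cannot see the mucosa. The Discussion presents both scales as physician-based assessments, which an ordinary call does not provide.

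Three things are at stake. First, the WHO outcome and the weekly distributions would combine examined grades during radiotherapy with unexamined reports afterwards, and the change of method falls where recovery is measured. Second, participants know their allocation. Section 3.4 keeps the assessor unaware of the arm, but that does not blind a self-report. Third, a Grade 0 reported by telephone could end a participant's assessments without an examination.

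**Working it through.** **Inputs.** Radiotherapy lasts 4–7 weeks (section 2.3.1). Follow-up continues for 6 weeks afterwards (section 6.5). The assessment marks come from Table 2.

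**Duration.** 4 + 6 = 10 and 7 + 6 = 13 weeks, which reproduces the 10–13 weeks in section 2.4.2.

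**Marks falling after radiotherapy.** For a course of R weeks, the post-radiotherapy weeks are W(R+1) to W(R+6). A blood test is taken as the scheduled item that implies attendance, since section 4.4 places the tests at the cancer centre.

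| R | Post-radiotherapy weeks | WHO marks | Blood tests | WHO marks without blood test | Share of all weekly WHO gradings | RTOG marks | RTOG marks without blood test |
|---|---|---|---|---|---|---|---|
| 4 | W5–W10 | 6 | W8 | 5 | 5/10 = 50% | W5–W8 | 3 |
| 5 | W6–W11 | 6 | W8 | 5 | 5/11 = 45% | W6–W8 | 2 |
| 6 | W7–W12 | 6 | W8 | 5 | 5/12 = 42% | W7–W8 | 1 |
| 7 | W8–W13 | 6 | W8, W13 | 4 | 4/13 = 31% | W8, W13 | 0 |

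These are counts for participants who do not recover early. Recovery stops assessment, so the actual numbers will be lower.

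**The six-week point.** It falls at W10, W11, W12 and W13 for courses of 4, 5, 6 and 7 weeks. The W13 marks for RTOG and blood tests therefore coincide with six weeks after radiotherapy only for 7-week courses.

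**Direction of error.** Let p be the true proportion with WHO Grade 3 or above in a given week, and q the proportion of the others wrongly graded that high. The observed proportion is p + (1 − p)q.

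- Equal q in both arms: the observed difference is the true difference times (1 − q), so it shrinks. With assumed true rates of 30% and 15%, q = 0.1 gives 37% and 23.5% (13.5 points instead of 15), and q = 0.3 gives 51% and 40.5% (10.5 points).
- Unequal q: with an assumed true rate of 30% in both arms, q = 0.1 in one and 0.2 in the other gives 37% and 44%. This is a false difference of 7 points, whose sign depends on which arm has the larger q.

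All these rates are assumptions. The documents give none of them, so the example shows only that either direction is possible.

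**The case against.** The strongest reply is that the protocol never says a WHO grade is assigned by telephone. The signs of attendance listed above, with the blood tests at W8 and W13, suggest that some grading could be done in person. This stands as far as it goes. A reader might infer that all six post-radiotherapy grades come from calls, and the documents do not support that. But they also do not say that the mucosa is examined at any of those attendances, and three sections name the telephone.

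A reader might also infer that a telephone grade would rest on diet alone. That is too strong. Soreness and sores can be reported, and Table 3 limits Grade 3 to a liquid diet caused by mucositis, so a caller can ask the reason. The accurate description is unverified self-report.

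Nor does the protocol itself warn against telephone grading. Section 4.1 does say that restricted intake can distort the WHO scale, "which could result in overestimation of the grade, such as categorizing the condition as Grade 3 despite the absence of corresponding clinical findings", but this concerns nasogastric feeding, and those cases are recorded as not applicable. The mechanism is related, but the warning is not about calls.

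Finally, a stated loss of power would not be supported. It would rest on assumed rates at a single week, and section 4.5 uses the weekly grades to describe trends. Section 1.1 places peak severity at 66–70 Gy. For high-dose courses that is near the end of radiotherapy, when grades are examined. If the WHO outcome is read as ever reaching a severe grade, a false high grade by telephone matters only for participants not already graded severe. This limits the effect on occurrence, but not on the recovery comparison or the recovery rule.

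**Conclusion.** The concern holds as a conflict between the instrument and the stated mode of contact. As written, four or five of the six WHO gradings after radiotherapy (31% to 50% of all weekly WHO gradings) have no laboratory test in the same week to imply attendance. This assumes that blood tests are done in person, that no participant recovers early, and that no further visits take place. Further visits are possible under the text but are not scheduled.

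The problem is not confined to WHO. For courses of 4 to 6 weeks, one to three RTOG marks fall after radiotherapy without a blood test in the same week, inside the window of the primary outcome. The exposure there is smaller, because RTOG Grades 1 to 3 in Table 3 also carry a pain or analgesic descriptor that can be reported. The recovery rule needs Grade 0 on both scales, so it is affected too.

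The documents do not give the size or direction of the bias. Equal error in both arms would dilute a difference, while self-report by unblinded participants could move it either way. This is worth correcting now because recruitment has started.

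**What to change.** - **Sections 4.1, 6.5 and Table 2:** state which post-radiotherapy contacts are attended and which are by telephone. Index them to weeks since the end of radiotherapy, not to W13. Bring sections 2.4.3, 4.2 and 4.3 into line.
- **Grading:** assign WHO and RTOG grades, and declare recovery under section 2.4.2, only at attended examinations.
- **Telephone contacts:** record diet (with the reason for any restriction), soreness and reported sores as separate self-reported items. Do not convert them to a grade.
- **Sections 2.5, 4.1 and 4.5:** restrict the WHO outcome and the weekly grade distributions to examined grades. Record the mode of contact for grades already collected so that this restriction can be applied.

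The cost is mainly wording, submitted as an amendment under section 6.2. The price in information is coarser timing of recovery between attended visits. Some participants may also stay under assessment until the next examination confirms recovery.
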